##### Endpoints

The primary trial endpoint will be a change in Hb concentration, measured by HemoCue®, on the day of inclusion, and post‐intervention at the end of malaria transmission season, that is, 1 month after the last SMC cycle. The secondary endpoints will include incidence of clinical malaria, defined as fever of >37.5°C or a history of fever in the preceding 48 h, and a positive malaria blood film of any parasite density, detected by passive case detection during the surveillance period; change in prevalence of anaemia between the day of inclusion and post‐intervention at the end of malaria transmission season (anaemia will be defined as an Hb less than 11 g/dL); the incidence of solicited adverse events and adverse drug reactions assessed to be related to the study medications during a period of six consecutive days after administration of study drugs; prevalence and density of *Plasmodium falciparum* infection at the post‐intervention survey; prevalence and density of helminth infection; and prevalence and density of malaria‐helminth co‐infection at the post‐intervention survey. Tertiary endpoints will include the cost per child treated per year and the cost per anaemia case averted calculated by a cost analysis, and the incidence of anaemia among the children in the intervention and control arms will be used to estimate the incremental cost‐effectiveness of integrated SMC plus anthelminthic treatment versus SMC alone, in terms of incremental economic costs per DALY averted (Box 1).

BOX 1Study medications.Given that this study will be implemented during an SMC campaign and in collaboration with the SMC programme of the Ghana Ministry of Health, the SMC drugs will be obtained from the SMC implementation unit of the Ministry of Health. The ALB and PZQ for this study will be procured from GlaxoSmithKline and Merck, respectively. Vitamin A will be a liquid, oil‐based preparation of retinyl palmitate or retinyl acetate, obtained from the United Nation's Children Fund, Ghana office. The zinc preparation will be a citrus‐flavoured tablet containing 25 mg Zn in the form of zinc sulfate and will be obtained from Biolectra Zink; Hermes Arzneimittel GmbH, Munich, Germany. To minimise under‐and over‐dosing while keeping simple dosage recommendations, the doses of SP and AQ for SMC, anthelminthics, vitamin A and zinc supplement will be based on the child's age, as follows:SP tablet (500 mg sulphadoxine + 25 mg pyrimethamine): Children aged 5–10 years will receive two tablets as a single dose on the first day.AQ tablet (153 mg base): Children aged 5–10 years will receive two tablets as a single dose for 3 consecutive days.ALB tablet (200 or 400 mg depending on age): Children aged 5–10 years will receive a single dose of ALB 400 mg.PZQ tablet (600 mg): Children aged 5–10 years will receive PZQ based on their body weight of 40 mg/kg.Vitamin A oral liquid (200,000 IU): Children aged 5–10 years will receive 200,000 IU vitamin A.Zinc tablet (40 mg/kg): Children aged 5–10 years will receive zinc supplement based on their body weight of 40 mg/kg.
The medications will be administered to the study children by a member of the SMC and NTD control programme staff in the presence of the study investigator and parents/caregivers of the children. The investigator will ensure that blood, urine and stool samples have been collected from the child before administration of the study drugs.Given that the toxicities caused by interactions of PZQ with ALB are dose‐dependent and can be reduced by taking PZQ with carbohydrate meals [28], PZQ will be given to the children based on the dose recommended by WHO, which is dependent on the body weight of the child (40 mg/kg). We will ensure that the children take carbohydrate‐rich meals by providing them healthy snacks before the administration of the drugs. If the child vomits, we will wait for 30 min and then try again. If vomiting occurs a second time, the medication will not be repeated, and the child will not be enrolled in the study. If the drug‐causing problems are ALB or PZQ, then the child will continue to receive the SMC drugs. If a child misses one of the SMC drugs at a round, the child will continue to receive further doses, in line with the SMC implementation guidelines. Children who start treatment but could not be found at home after reasonable efforts will be excluded from the study. A simple, user‐friendly recording tool will be used to capture the drug administration for each child.

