## METHODS

### Study design

This will be a cluster randomised, controlled, programme‐led pragmatic study to evaluate the effectiveness of co‐administration of SMC and MDA for schistosomiasis and STH in reducing anaemia due to malaria‐helminth co‐infections among school‐age (5–10 years old) children. The trial has been registered on Clinicaltrials.gov NCT06182176 and Pan‐African Clinical Trials PACTR202312489417172. The interventions for this study are the WHO‐approved drugs for preventive treatment of malaria (sulphadoxine‐pyrimethamine [SP] + amodiaquine [AQ] [SPAQ]) [10], and helminths (ALB and PZQ) [11]. These interventions will be delivered jointly by the Ghana Health Service‐led SMC and NTD control programmes, to the children enrolled in this study. The children will be enrolled at community levels and the communities will be assigned into two equal clusters, to receive either combined SMC and anthelminthic drugs or SMC drugs only. To minimise the potential for contamination and spill‐over effect, the study communities will be separated from each other by at least 5 km. To ensure objectivity in the reporting of adverse events among the children across the two clusters, vitamin A and zinc supplement will be given to children in the control clusters randomised to receive SMC drugs only. This approach will ensure that children in the intervention and control clusters receive three drugs. Vitamin A and zinc supplements have not been shown to affect the outcomes of this study [12, 13].

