
##### Intervention stage

Given that the focus of this project is to evaluate the effectiveness of the integrated SMC‐MDA control programmes, the first day of starting the intervention stage (Day 0) will correspond to the day prior to the commencement of the first cycle of SMC in the study area. On Day 0, the communities will be randomised at community level into two clusters at 1:1 ratio to receive either combined SMC and anthelminthic drugs (intervention cluster) or SMC drugs only (control cluster). Given that 4‐aminoquinoline drugs are reported to have antagonistic pharmacological interactions with PZQ [23], the SMC partner drugs, AQ (a 4‐aminoquinoline derivative) and SP will not be administered with anthelminthic drugs (ALB and PZQ) on the same day in this study. Therefore, eligible children randomised into the intervention clusters will receive ALB and PZQ on Day 0 and those randomised into the control clusters will receive vitamin A and zinc supplement as control drugs on this day. On the following day, which corresponding to the start (Day 1) of the first SMC cycle, the children in the control and intervention clusters will receive SPAQ according to the WHO and Ghana SMC implementation guidelines. This will be followed on the second and third day of the SMC cycle with all study children in the two groups receiving AQ, in line with the SMC guidelines [5]. The study will administer AQ on Days 2 and 3 to the children in the presence of their parents/caregivers. Trained field workers will visit all enrolled children daily, irrespective of the study arms, at home starting from the evening of Day 0 till 3 days after completion of the first cycle of SMC course, using a purpose‐designed electronic diary card, to collect adverse drug reactions and adverse events such as vomiting, skin rash, body weakness, etc. Trained research assistants will visit each child 1 month after each round of SMC cycle to check that there are no severe reactions to the previous treatment and to give the next round of treatment (Table 1).

**TABLE 1 tmi14062-tbl-0001:** Schematic diagram of the study procedures for the effectiveness study.

SMC cycle	1					2, 3 and 4	End of malaria season (i.e., 1 month after completion of the last SMC cycle)
Timelines (days)	Pre‐intervention survey	Day 0	Day 1	Days 2 and 3	Days 4–6		Post‐intervention survey

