### Statistical analysis plan

The field and laboratory data will be merged, harmonised, cleaned and analysed with STATA® version 18.1 SE (Stata Corp., College Station, TX, USA). Descriptive statistics such as frequencies and proportions will be used to summarise the baseline parasitic parameters and socio‐demographical characteristics of the study participants by cluster arm. Data will be analysed using an ITT approach. The proportions of adverse events and the incidence (average number per participant) of reported adverse events will be compared between the study groups using the Chi‐squared test. Logistic regressions with robust standard errors will be used to estimate odds ratios and 95% confidence intervals. Wald tests will be used to assess the evidence of difference in odds between study groups, after controlling for baseline characteristics (sex, age group, weight and malaria and helminth infections' occurrence). Effect modification between intervention period and study groups will also be investigated using the Wald test. The geometric means of the *P. falciparum*, STH and schistosome intensities will be estimated and plotted before and after intervention periods. A univariable Poisson regression with robust standard error and Wald test will be used to compare the pre‐intervention parasites intensities across groups, and a multivariable Poisson regression including the pre‐intervention parasites intensities as a covariate, adjusting for other baseline characteristics described above, and Wald test will be used to compare the post‐intervention parasites intensities. The proportions of adverse events and the incidence (average number per participant) of reported adverse events will be compared between the study groups using the Chi‐squared test. All statistical tests will be two‐sided at a significance of *α* <0.05.

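### The safety endpoint appears limited to treatment-related events while the planned analysis compares all reported events, so the event set for the between-arm comparison is not fixed

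*Protocol article*

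**What the plan says.** The protocol article describes the safety outcome in four places.

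- **Endpoints.** A secondary endpoint is "the incidence of solicited adverse events and adverse drug reactions assessed to be related to the study medications", counted "during a period of six consecutive days after administration of study drugs".
- **Statistical analysis plan.** "The proportions of adverse events and the incidence (average number per participant) of reported adverse events will be compared between the study groups" with a chi-squared test. The sentence appears twice in that section, and neither occurrence mentions relatedness.
- **Intervention stage.** Field workers visit every enrolled child in both arms daily, from the evening of Day 0 until three days after the first SMC course, "to collect adverse drug reactions and adverse events such as vomiting, skin rash, body weakness" and so on, on an electronic diary card. Table 1 marks safety assessments from Day 0 to Days 4–6.
- **Study design.** "To ensure objectivity in the reporting of adverse events among the children across the two clusters, vitamin A and zinc supplement will be given" to control children, so that each arm receives three drugs.

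On who can see the allocation, Box 1 lists albendazole and praziquantel tablets for the intervention arm, and an oil-based vitamin A liquid and a citrus-flavoured zinc tablet for the control arm. Programme staff give them "in the presence of the study investigator and parents/caregivers of the children". Randomisation is by community. The only masking stated is that of laboratory staff, under Pre-intervention stage.

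**The concern.** The endpoint and the analysis seem to describe different sets of events. If the endpoint is related events only, the stated analysis does not estimate it. If the analysis is right, the endpoint is misdescribed. Either comparison could later be reported as the planned one.

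The choice matters because the two versions are exposed to bias differently. A related-only count passes each event through a causality judgement. Where the person judging knows the arm, that judgement may differ between arms even if the events do not. Giving both arms the same number of products does not conceal a liquid from a tablet, so the safeguard described under Study design does not settle this. Tolerability of adding the anthelminthics bears on scale-up, which the Discussion names as an aim.

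**Working it through.** **1. Plan's own figure.** There is none for this endpoint. The sample size of 1200 rests on haemoglobin and is unaffected.

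**2. Which events does the endpoint count?** The phrase in Endpoints can be read in two ways.

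- *Reading A:* the relatedness qualifier covers both solicited events and drug reactions. This is the more natural reading, because the six-day window that follows it must apply to both nouns. The endpoint then conflicts with the unfiltered comparison in the Statistical analysis plan section.
- *Reading B:* the qualifier covers only drug reactions. All solicited events are then counted, which agrees with the analysis and with the two categories on the diary card. The qualifier is nearly redundant, since a reaction already implies relatedness, and the analysis section names no separate comparison of reactions.

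The text needs rewording under either reading.

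**3. What would a related-only count do?** Let p be the true risk of a solicited event, equal in both arms, and let a₁ and a₀ be the probabilities that an event is called related in intervention and control. With one event per child, the related-event risks are p·a₁ and p·a₀, and their ratio is a₁/a₀ whatever p is. The documents give neither p nor a, so these values are assumptions:

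| a₀ | a₁ | ratio a₁/a₀ |
|---|---|---|
| 50% | 50% | 1.00 |
| 50% | 60% | 1.20 |
| 50% | 70% | 1.40 |
| 40% | 80% | 2.00 |

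The direction is assumed too. Exchanging the second row (60% in control, 50% in intervention) gives 0.50/0.60 = 0.83.

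For scale, take p = 30% with 50% against 70%. The related-event risks are 0.30 × 0.50 = 15% and 0.30 × 0.70 = 21%. With 600 independent children per arm, the chance of p < 0.05 is about 77%. If the haemoglobin design effect is borrowed, 1 + 59 × 0.05 = 3.95, the effective size is 600/3.95 = 151.9 per arm and the chance is about 27%.

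**4. Allowing for SPAQ in both arms.** Both arms receive SPAQ on Day 1 and AQ on Days 2 and 3. Suppose attribution differs only for events on Day 0, which are a fraction f of all events, and equals a₀ otherwise. The ratio becomes 1 + f(a₁/a₀ − 1). If events were spread evenly over Days 0 to 6, f = 1/7 and the ratios 1.20, 1.40 and 2.00 shrink to 1 + 0.20/7 = 1.03, 1 + 0.40/7 = 1.06 and 1 + 1.00/7 = 1.14. With f = 1 they stay as tabulated. The true f is unknown.

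**5. All-event count.** No attribution step enters, so with equal true and reported risk the ratio is 1.00.

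**The case against.** The strongest reply is that Reading B makes Endpoints, Intervention stage and Statistical analysis plan agree, so only a phrase needs tidying. The stated analysis already compares all reported events, and the diary discards none. That stands in part: the conflict depends on the reading, and an all-event comparison is available as the plan is written. It does not show which set is the endpoint.

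A reader might infer that people who know the arm will apply a relatedness filter and so bias the safety comparison irreparably. The documents do not support this. They do not say who assesses relatedness or whether that person is masked, and a condensed article may leave this to the full protocol. The diary field workers are not listed as present at dosing, and an independent board oversees safety. That staff and parents can tell the arms apart is a strong inference, not a statement in the text. It rests on unlike products, allocation by community, who is present at dosing, and a rule in Box 1 that presupposes knowing the child took albendazole or praziquantel. Because the diary keeps every event, any attribution bias can be avoided by counting them all.

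The reply about SPAQ also stands: for most of the window a control child's event can be attributed to a study drug too, which narrows any gap. Finally, safety is one of several secondary endpoints, and the Introduction and Discussion cite an earlier trial in Senegal on safety and tolerability.

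**Conclusion.** The point holds in a limited form. On its natural reading the endpoint is related-only, the stated analysis is not, and the event set for the between-arm safety comparison is therefore not fixed. If the related-only version were used, the result could reflect attribution as well as tolerability. This assumes that the assessor knows the arm, which is likely from the text but not stated.

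The size of any bias cannot be derived from the documents. The illustrative ratios of 1.03 to 2.00 only restate the assumed attribution gaps and the assumed share of events open to them; the direction could be reversed and the gap could be nil. The primary haemoglobin endpoint and the sample size are untouched. The change is still worth making, because it costs almost nothing and removes both the ambiguity and this one source of bias.

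**What to change.** - **Endpoints:** define the safety endpoint as the incidence of all solicited adverse events recorded on the daily diary in the stated surveillance window, regardless of assessed relationship to study medication.
- **Statistical analysis plan:** name that event set as the one compared between arms, and state the comparison once. Report assessed relatedness descriptively only, saying who assesses it and whether that person is masked.
- **Study design:** soften the statement introduced by "To ensure objectivity in the reporting of adverse events among the children across the two clusters". The supplements equalise the number of products but do not conceal the arm. An all-event endpoint removes attribution bias; it does not remove reporting bias from parents who know the arm, for example for a subjective symptom such as body weakness.

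No new data are needed, since the diary already covers every child in both arms. The downside is that more background events enter the count, which may dilute a real difference somewhat.

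### Box 1 prints the control-arm zinc dose as 40 mg/kg for a 25 mg tablet, which is 1.6 tablets per kg and cannot be right

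*Protocol article*

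**What the plan says.** All the dosing text is in Box 1 (Study medications) of the protocol article, within the Endpoints section.

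- **Product.** The zinc preparation is a "tablet containing 25 mg Zn in the form of zinc sulfate".
- **Dose.** The zinc line gives 40 mg/kg in brackets after the tablet name, where the SP, AQ, ALB and PZQ lines give a strength. It then says that children aged 5–10 years "will receive zinc supplement based on their body weight of 40 mg/kg".
- **Dosing principle.** The lead-in to the list aims to limit under- and over-dosing "while keeping simple dosage recommendations". It says that the "doses of SP and AQ for SMC, anthelminthics, vitamin A and zinc supplement will be based on" the child's age.
- **PZQ.** The line for the 600 mg tablet reads "Children aged 5–10 years will receive PZQ based on their body weight of 40 mg/kg". The text after the list repeats this weight-based dose for PZQ as the WHO recommendation.

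The Intervention stage section says who takes zinc and when. On Day 0, "those randomised into the control clusters will receive vitamin A and zinc supplement as control drugs on this day".

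**The concern.** A per-kilogram figure cannot be a tablet strength, so the bracketed label is wrong whatever dose was intended. The dosing sentence is a separate problem: a 25 mg tablet and a 40 mg/kg dose do not exclude each other logically, but the resulting number of tablets is not one that could be given to a child. It also defeats the aims stated in the lead-in, which are simple dosing by age and avoidance of over-dosing.

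This is the only zinc dose in the article, and it applies to every control child. The Pre-intervention stage section has each child weighed, so staff could apply a per-kilogram rule if they took the line at face value. Zinc and vitamin A are there to keep adverse-event reporting objective between the arms (Study design), and adverse events are a secondary endpoint (Endpoints). If children were dosed as printed, safety would be at risk and the adverse-event comparison would be distorted. If they were not, readers still cannot tell from the article what the comparator was.

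**Working it through.** **Inputs**
- Zinc tablet: 25 mg Zn (Box 1).
- Zinc dose as printed: 40 mg/kg (Box 1, given twice).
- PZQ: 600 mg tablet, 40 mg/kg (Box 1).
- Control children: 10 schools with a minimum of 60 children each (Sampling for the intervention stage).
- Body weight: not given in the article. I assume 15 to 30 kg, with 12 to 40 kg as a wider range.

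The article states no tablet count, so there is no derived figure to reproduce. The check is whether dose and product fit together.

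**Without any weight assumption**
- Tablets per kg = 40 / 25 = 1.6.
- Weight at which one tablet delivers the printed dose = 25 / 40 = 0.625 kg.

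**At assumed weights**

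Dose = 40 × weight; zinc tablets = dose / 25; PZQ tablets = dose / 600.

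| Weight (kg) | Dose at 40 mg/kg (mg) | Zinc tablets (25 mg) | PZQ tablets (600 mg) |
|---|---|---|---|
| 12 | 480 | 19.2 | 0.8 |
| 15 | 600 | 24 | 1.0 |
| 20 | 800 | 32 | 1.3 |
| 25 | 1000 | 40 | 1.7 |
| 30 | 1200 | 48 | 2.0 |
| 40 | 1600 | 64 | 2.7 |

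The same rule is workable for PZQ and unworkable for zinc across the whole range. For scale, one 25 mg tablet is 25 / 30 = 0.83 mg/kg at 30 kg and 25 / 15 = 1.67 mg/kg at 15 kg.

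**Other readings of the line**
- *A flat 40 mg, with the per-kilogram unit a slip.* 40 / 25 = 1.6 tablets, which is not a practical dose of this product.
- *40 mg/kg of zinc sulfate salt rather than of zinc.* The article gives no salt weight. If zinc is assumed to be 23% to 40% of the salt by mass, one tablet holds 25 / 0.40 = 62.5 mg to 25 / 0.23 = 108.7 mg of salt. The count is then 600 / 108.7 = 5.5 tablets (15 kg) to 1200 / 62.5 = 19.2 tablets (30 kg), still far from simple dosing.
- *Dosing by age, as the lead-in says.* The zinc line itself says body weight.

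**Lead-in against the six drug lines.** SP, AQ, ALB and vitamin A each have one fixed dose for ages 5–10, which fits the lead-in. PZQ and zinc are given per kilogram, which does not. For PZQ the weight basis is confirmed later in the box, so only the lead-in is loose. For zinc nothing else in the article supports 40 mg/kg.

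**Children concerned.** 10 × 60 = 600 at minimum.

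**The case against.** The strongest reply is that this is a misprint in a condensed article. The dose actually used would come from the full protocol and dosing chart, and the Ethical considerations section reports approval by three ethics committees and the national regulator. The zinc sentence looks copied from the PZQ sentence, and the same box gives the product strength correctly. Programme staff give the drugs with the study investigator present, and a "recording tool will be used to capture the drug administration for each child". There is also external monitoring and an independent safety board. Dozens of tablets for one child would hardly go unnoticed. No estimand, analysis or power statement depends on the zinc dose.

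Most of this stands as a limit on what can be claimed about conduct. Harm is conditional, and the document does not show it. None of it makes the printed line correct. Nor is this a detail left to a fuller document: the article chose to state a dose and stated one that cannot be followed. That the figure is printed twice in the line also makes a text-extraction fault unlikely. Two smaller points are fair: the defect is an inconsistency between dose and product rather than a miscalculation, and the loose lead-in for PZQ is editorial and adds no weight.

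**Conclusion.** The concern holds. The zinc line in Box 1 is wrong as printed, both as a strength and as a dose. The size of the error is 1.6 tablets per kg, which needs no assumption. The range of 24 to 48 tablets rests on assumed weights of 15 to 30 kg, but the dose is unworkable at any plausible weight for ages 5–10. Carry-over from the PZQ line is the likely cause, though this is not proven.

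Because it is the only stated dose of a drug to be given to at least 600 children, it must be corrected on safety grounds alone. The adverse-event comparison is affected only if children were dosed as printed, which the article does not establish. Sample size and power are untouched.

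**What to change.** 1. Check Box 1 against the approved protocol and dosing chart.
2. In the zinc line, remove 40 mg/kg from both places. Print the strength as 25 mg and state the approved dose, as a number of 25 mg tablets by age if that is what the approved documents say. Deleting only the per-kilogram unit does not repair the line. The article gives no basis for deriving the correct dose, and none is proposed here.
3. Amend the lead-in so that doses follow the child's age, except PZQ, which is given at 40 mg/kg body weight.
4. If the approved protocol or dosing chart carries the same zinc figure, correct it there and notify the ethics committees, the regulator and the safety board.
5. If dosing has started, check the zinc dose actually given in the drug administration records.

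The first three steps cost a document check and a short published correction. The last two apply only under the conditions stated.

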### Sample size determination

We assumed that the mean Hb concentration in the SMC alone group will be 10.5 g/dL with a standard deviation of 1.5 g/dL [3]. Assuming an intra‐class correlation coefficient of 0.05, then 10 communities per cluster, a study of 60 children per community will have 80% power to detect an increase in mean Hb of 0.5 g/dL (to 11.0 g/dL) in the SMC plus anthelminthic group as statistically significant at 5% level. A minimum sample size of 1200 school‐age children (5–10 years) will be enrolled. This study will be implemented in three stages: pre‐intervention, intervention and post‐intervention. The pre‐intervention survey will be conducted to determine the prevalence of malaria‐helminth co‐infection in the study population.

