##### Post‐intervention stage

All child participants enrolled in the intervention study will be evaluated 1 month after the last course of SMC, which corresponds to the end of malaria transmission season, to measure their Hb concentration and to obtain a further blood film, dried blood spot, stool and urine samples, to test for malaria‐helminth co‐infections using parasitological methods such as microscopy, Kato‐Katz, urine filtration test and improved diagnostic tools including molecular methods (quantitative polymerase chain reaction), as described above.

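### Box 1 removes children after randomisation and first dosing, against the stated intention-to-treat analysis, and the vomiting rule can do so unequally by arm

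*Protocol article*

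**What the plan says.** Box 1 (Study medications, printed under Endpoints) holds two removal rules. On vomiting: "If vomiting occurs a second time, the medication will not be repeated, and the child will not be enrolled in the study". On absence: "Children who start treatment but could not be found at home after reasonable efforts will be excluded from the study". Box 1 adds that SMC drugs go on being given where albendazole (ALB) or praziquantel (PZQ) is the cause, and that a child who misses an SMC drug in one round carries on with later doses.

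The Statistical analysis plan section says: "Data will be analysed using an ITT approach". The cost-effectiveness section also takes its effect measure from ITT results. The Post-intervention stage section says: "All child participants enrolled in the intervention study will be evaluated 1 month after the last course of SMC". The Intervention stage section sends field workers daily to all enrolled children in both arms, from the evening of Day 0 until three days after the first SMC course, to record adverse events. Vomiting is the first example it names.

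**The concern.** An ITT comparison rests on keeping the children whom randomisation placed in each arm. Both Box 1 rules take children out on the basis of something that happens after allocation. If the trigger is related to the allocated drugs, the children left in the two arms are no longer comparable.

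Two endpoints are exposed. The first is safety: a child declared not enrolled at dosing falls outside visits defined for enrolled children, and the event behind the removal is one the trial means to count. The second is the primary endpoint, change in Hb: a removed child may have no final measurement, and no later analysis can recover it.

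**Working it through.** **Order of events.** Table 1 puts consent and enrolment at the pre-intervention survey, and randomisation and intervention on Day 0. The Intervention stage section randomises communities on Day 0 and gives ALB + PZQ or vitamin A + zinc that same day. A second vomit, or a failure to find a child who has started treatment, can therefore occur only after allocation. Even if enrolment were taken to be complete only once the Day 0 drugs are kept down, the rule would still select children on their response to the allocated drugs.

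**Which rule can depend on arm.**
- Vomiting rule: the Day 0 drugs differ by arm, and Box 1 itself refers to toxicities from PZQ given with ALB. Removal can follow from the allocated treatment.
- Not-found rule: the same words apply to both arms, and nothing in the document shows that it acts differently between them. It still conflicts with ITT. It also sits beside the missed-dose rule without saying which applies when absence is the reason for the missed dose.

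**The plan's own power figure.** Inputs from Sample size determination: "the mean Hb concentration in the SMC alone group will be 10.5 g/dL with a standard deviation of 1.5 g/dL"; "a study of 60 children per community will have 80% power to detect an increase in mean Hb of 0.5 g/dL"; ICC 0.05; 10 communities per arm; 5% level. The Statistical analysis plan section adds: "All statistical tests will be two‐sided".
- Design effect = 1 + (60 − 1) × 0.05 = 3.95.
- Effective n per arm = 600 / 3.95 = 151.9.
- Standard error of the difference = 1.5 × √(2 / 151.9) = 0.172 g/dL.
- Power = 82.8% (normal approximation), or 78.4% (noncentral t, 2 × 10 − 2 = 18 df). The stated 80% is reproduced.
- With 10% loss (54 per community), power is 81.8% or 77.4%. With 20% loss (48 per community), it is 80.5% or 76.1%.

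Loss by itself costs little power. The issue is bias.

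**Bias in Hb change.** Let p1 and p0 be the shares excluded in the intervention and control arms. Let g be the amount by which the mean Hb change of excluded children lies below that of retained children, taken as equal in both arms. Each retained mean is too high by p × g, so the bias in the arm difference is (p1 − p0) × g. The documents give none of these quantities, and all values below are assumptions.

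| Excluded, intervention vs control | g = 0.5 | g = 1.0 | g = 1.5 g/dL |
|---|---|---|---|
| 2% vs 0% | 0.01 | 0.02 | 0.03 |
| 5% vs 1% | 0.02 | 0.04 | 0.06 |
| 10% vs 2% | 0.04 | 0.08 | 0.12 |
| 15% vs 5% | 0.05 | 0.10 | 0.15 |

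Against the 0.5 g/dL target this is 0.01 / 0.5 = 2% up to 0.15 / 0.5 = 30%. If excluded children do worse, the intervention looks too good; if they do better, the sign reverses. The bias is zero when g = 0, or when exclusions are alike in number and type in the two arms.

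**Vomiting risk difference.** With true risk v and share e removed for vomiting twice, the observed risk is (v − e) / (1 − e). The rates are again assumed.
- True 10% vs 3%, removed 3% vs 0.5%: 0.07 / 0.97 = 7.2% and 0.025 / 0.995 = 2.5%. The difference falls from 7.0 to 4.7 points.
- True 10% vs 5%, removed 5% vs 1%: 0.05 / 0.95 = 5.3% and 0.04 / 0.99 = 4.0%. The difference falls from 5.0 to 1.2 points.

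**The case against.** A reader might infer that both rules lose children differently by arm, so that the Hb and safety comparisons are both biased. The document does not support that much.
- The not-found rule makes no distinction between arms. Much of what it covers is ordinary loss to follow-up, where no final Hb would exist under any wording.
- Box 1 lets children with ALB or PZQ problems continue SMC drugs. They may be meant as an exception who stay in the trial, so it is not settled that children who did not tolerate the added drugs leave the intervention arm.
- Nothing says that recorded events will be deleted. Box 1 provides a tool for recording each child's drug administration, and children who vomit once are unaffected, so the safety difference shrinks rather than vanishes.
- The endpoint is change in Hb. A gap of 1.0 g/dL in change is already twice the target effect, so the right-hand columns of the table are generous to the concern.

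These points stand and limit the claim. They do not remove the conflict. Continuing SMC drugs does not say that the child remains in follow-up or analysis. Nor can the matter be left to a fuller analysis plan: detailed set definitions may belong there, but here explicit rules contradict each other, and a plan written later cannot restore visits and measurements that were never made.

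**Conclusion.** The contradiction holds: Box 1 removes children after randomisation and dosing, while the analysis, the economic evaluation and the final survey assume that they are kept. The vomiting rule is the stronger half, because its trigger can be an effect of the allocated drugs and is itself a safety outcome. For the not-found rule, only the conflict with ITT is shown.

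Bias in Hb change is possible and probably small. At a gap of 0.5 g/dL it is 0.01 to 0.05 g/dL, and it reaches 0.15 only at the extreme of the assumed range. The vomiting comparison could be weakened materially, but by how much depends wholly on rates that the documents do not give. The repair is worth making before follow-up starts, because it is cheap and the lost data cannot be recovered.

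**What to change.** Replace only the closing clause of the vomiting sentence (on enrolment) and the closing clause of the not-found sentence (on exclusion). Leave the clinical text on repeat dosing untouched. State instead that:

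1. Every consented, eligible child in a randomised community who reaches the first Day 0 dose, including any reserve-list replacement, stays in the ITT set and is sought for the post-intervention survey, whatever doses were taken or retained. Starting the set at this point respects the acute-illness criterion, which is judged at drug administration, and the reserve list in the sampling section.
2. Every child given any study drug stays in the safety set and the Day 0 to Day 6 visits, with vomiting counted as an adverse event.
3. Children who cannot be found are reported as lost to follow-up by arm, with a sensitivity analysis for missing Hb.
4. Exclusion for vomiting or absence applies only in a per-protocol sensitivity analysis.

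The sponsor should also reconcile the two Box 1 statements on a child who vomits ALB or PZQ, who is both not enrolled and continuing SMC drugs, and say whether that child remains in the study. No dosing rule is proposed here. The cost is a few sentences and a small number of extra safety and final-survey visits.
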